## Abstract

**Background:**

Oral feedback from clinical educators is the traditional teaching method for improving clinical consultation skills in medical students. New approaches are needed to enhance this teaching model. Multisource feedback is a commonly used assessment method for learning among practising clinicians, but this assessment has not been explored rigorously in medical student education. This study seeks to evaluate if additional feedback on patient satisfaction improves medical student performance.

**Methods:**

The Patient Teaching Associate (PTA) Feedback Study is a single site randomized controlled, double-blinded trial with two parallel groups.

An after-hours general practitioner clinic in Victoria, Australia, is adapted as a teaching clinic during the day. Medical students from two universities in their first clinical year participate in six simulated clinical consultations with ambulatory patient volunteers living with chronic illness. Eligible students will be randomized in equal proportions to receive patient satisfaction score feedback with the usual multisource feedback and the usual multisource feedback alone as control. Block randomization will be performed. We will assess patient satisfaction and consultation performance outcomes at baseline and after one semester and will compare any change in mean scores at the last session from that at baseline. We will model data using regression analysis to determine any differences between intervention and control groups. Full ethical approval has been obtained for the study. This trial will comply with CONSORT guidelines and we will disseminate data at conferences and in peer-reviewed journals.

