## Methods/design

### Study design

The Patient Teaching Associate (PTA) Feedback Study is designed as a randomized, controlled, assessor- and patient-blinded, single-centre exploratory trial with two parallel groups after six student consultation sessions (Figure 1). The CONSORT statement has been used as the framework for the methodology of this study.

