### Secondary outcome measures

The RICS is the secondary outcome measure. The performance score by tutors gives a composite score and subscale scores of patient-centred approach, history taking, physical examination and problem solving and management. Tutors receive standardization training based on a video and complete the assessments within 24 hours of the student consultation episodes. The RICS was chosen because it is a student performance assessment tool designed for the Patient Partnership Program, a similar teaching programme developed at the Launceston Clinical School, University of Tasmania [19, 20]. Its construct validity and psychometric properties have been reported [13]. The concurrent use of the RICS avoids the risk of a simple training effect on MISS-21 scores.

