### Allocation concealment and blinding

Allocation numbers are kept in sealed containers. Tutor and patient assessors will be blinded to group membership. Emergency unblinding will be considered only on student participants’ request and approval. For example, a student may experience significant distress and request tutor counselling or debriefing after receiving written feedback.

Tutor assessors, patient assessors and data analysts are blinded to group assignment of participants. Because of the nature of the feedback, student participants will not be blinded to the group membership.

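### The abstract's double-blinded label does not fit a trial whose students know their arm, and the unblinding example opens a one-sided route to the tutors who score RICS

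*Protocol article*

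**What the plan says.** The protocol article describes the masking in three places.

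- Abstract, Methods: the study "is a single site randomized controlled, double-blinded trial with two parallel groups".
- Study design: the trial is "randomized, controlled, assessor- and patient-blinded, single-centre exploratory trial with two parallel groups".
- Allocation concealment and blinding: "Tutor assessors, patient assessors and data analysts are blinded to group assignment of participants", followed by "Because of the nature of the feedback, student participants will not be blinded to the group membership".

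The last of these sections also sets the rule for breaking the blind: "Emergency unblinding will be considered only on student participants’ request and approval". Its example is that "a student may experience significant distress and request tutor counselling or debriefing after receiving written feedback".

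Three other sections bear on that example. Under Implementation, the intervention group gets its MISS-21 feedback at least a week before the final consultation, and the control group gets its own only after that consultation, within a month. Under Secondary outcome measures, tutors score the RICS. Under Adherence, participants with problems related to the intervention are told to contact the coordinator, and debriefing and referral for counselling are open to any student on request.

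**The concern.** There are two separate issues.

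The first is the label. Someone who reads only the abstract will ordinarily take double-blinded to mean that the randomized participants do not know their arm. Here they do. They are also the people whose performance is being rated, so awareness of the arm could itself affect how they prepare and behave. The abstract commits the trial to CONSORT reporting, and a label that the methods contradict would carry over into the results paper.

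The second is the unblinding example. The section that blinds tutors illustrates the exception with a student turning to a tutor about the written feedback, which is the very thing that distinguishes the arms. If that tutor later scores the same student's last RICS, the score is given with knowledge of the arm, and before the final session this can happen only in the intervention group. The RICS rests on a tutor's judgement. It also matters for interpretation, because the Secondary outcome measures section relies on it to guard against reading a simple training effect on MISS-21 as a real gain in skill.

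**Working it through.** No figure in the plan is in dispute. Its only calculation, the sample size, concerns MISS-21 and reproduces: n per group = 2 × (1.960 + 0.842)² × 0.46² / 0.32² = 32.4, rounded up to 33. Power at 33 per group is 80.7% by the normal approximation and 79.5% by the noncentral t distribution. The RICS was not used in that calculation, so the planned MISS-21 effect is no yardstick for a bias in RICS. The point itself is checked by comparing sections.

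**Label**

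| Party | Role | Masked, according to the blinding section |
|---|---|---|
| Students | randomized participants | no |
| Patients | rate MISS-21 (primary) | yes |
| Tutors | score RICS (secondary) | yes |
| Data analysts | analysis | yes |

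The Study design wording, "assessor- and patient-blinded, single-centre exploratory trial", agrees with this table. The abstract does not.

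**Unblinding route**

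1. Written feedback reaches the intervention arm at least one week before the last consultation (Implementation).
2. It reaches the control arm only after the last consultation (Implementation).
3. From 1 and 2, a request made before the last consultation and prompted by written feedback can come only from an intervention student. The subject of the request is enough to reveal the arm. A request prompted by oral feedback, which both arms receive, would not reveal it.
4. The example has the student asking for counselling or debriefing from a tutor, and tutors score the final RICS.
5. Nothing in the protocol article keeps the tutor who hears the request from scoring that student.

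The route therefore exists and runs in one direction. How often it would be used is not given.

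**Size**

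The bias in the mean RICS difference is f × b, where f is the share of intervention students whose scoring tutor has learned the arm and b is the resulting shift in score, in RICS standard deviations. The documents supply neither. As an illustration on assumed values only, take a true effect of zero, 33 per arm, and a two-sided 5% unpaired t test with noncentrality f × b × √(33/2):

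| f (assumed) | b (assumed) | f × b, in SD | Chance of a significant result |
|---|---|---|---|
| 0.10 | 0.25 | 0.025 | 5.1% |
| 0.10 | 0.5 | 0.05 | 5.5% |
| 0.25 | 0.5 | 0.125 | 7.9% |
| 0.50 | 0.5 | 0.25 | 17.0% |

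The distortion is small if such requests are rare and grows with their frequency. The sign of b is unknown: a tutor aware of a student's distress might score more kindly or more strictly.

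**The case against.** The label can be defended as shorthand for two masked rater groups, tutors and patients. A reader of the full Methods is not misled, since the blinding section lists every party and says openly that students are unmasked. That defence makes the label loose rather than the masking plan void, but an abstract reader cannot know that this meaning was intended.

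The unblinding route is narrower than it may first appear. It needs a student's request and approval, it is offered as an example, and the Adherence section already directs problems with the intervention to the coordinator. The article does not say that the counselling tutor scores the same student, and a fuller protocol may rule this out. These points limit how often the route would be used. They do not remove its one-sidedness, and the example as published still names a tutor.

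A reader might infer more than this, and three such readings are not supported:

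- That tutors learn the arm because they "complete the assessments within 24 hours of the student consultation episodes". The window applies equally to both arms and is an upper limit. It does allow scoring after the oral feedback talk, but that talk takes place in both arms under the same framework, and disclosure during it is conjecture.
- That the primary outcome is compromised. MISS-21 is rated by patients, who are stated to be blinded, and nothing in the debriefing or RICS rules tells them the arm.
- That the MISS-21 interviewer is unmasked. This argues from silence: the article calls that researcher independent, and the patient supplies the score.

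**Conclusion.** The concern holds in two limited parts. The abstract states a degree of blinding that the trial does not have, and the Study design and blinding sections show this without any assumption. The unblinding example, combined with the timing of written feedback in the two arms, is a route by which a tutor could learn that a student is in the intervention group before scoring the final RICS.

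The second part rests on the assumption that the tutor who hears the request may also be the one who scores, which the article neither states nor excludes. Any effect is on the secondary outcome, in one arm, with unknown direction and a size that the documents do not allow to be estimated. It is not a reason to doubt the blinding of the patients who rate MISS-21. Both parts should be corrected, as the remedy costs very little.

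**What to change.** - In the abstract, replace double-blinded with the Study design section's description (assessors and patients blinded), and add that students are not blinded.
- Reconcile the unblinding example with the Adherence section: before the final session, have requests for debriefing about written feedback taken by the coordinator or by a tutor who does not score that student. Support for students stays fully available.
- Log every case in which a scoring tutor learns a student's arm before the final RICS, with the date, so that the number can be reported.
- Optionally, have tutors complete the RICS form before the oral feedback at the last session. This is a precaution and does not imply that the 24-hour limit reveals the arm.

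The cost is a few changes of wording, a simple log, and occasional time from the coordinator or a non-scoring tutor. The optional step would briefly delay oral feedback that the Interventions section describes as immediate. Sample size and planned analyses are unchanged.

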**Discussion:**

This is the first proposed trial to determine whether consumer feedback enhances the use of multisource feedback in medical student education, and to assess the value of multisource feedback in teaching and learning about the management of ambulatory patients living with chronic conditions.

**Trial registration:**

Australian New Zealand Clinical Trials Registry (ANZCTR): ACTRN12613001055796.

## Background

Multisource feedback is a strong motivator in modifying clinicians’ behaviour and promoting reflective practice [1, 2]. Feedback may facilitate more accurate assessment of clinicians’ own skills by providing them with information that they may have unintentionally overlooked or underemphasized, and by identifying problems that could jeopardize patient satisfaction in a clinical consultation [3, 4].

Routine feedback to clinicians has been shown to improve client outcomes at the end of trainees’ practicum training, compared with no feedback [4, 5]. Although multisource feedback is the accepted workplace assessment of professional behaviours in training doctors [6–8], this form of assessment and feedback is not commonly integrated into medical student education. Central to this multisource feedback model is direct, immediate feedback from patients, peers and tutors to students, formally integrating multisource feedback into the teaching episode.

Interpersonal and communication skills in clinical consultations have been identified as a core competency in physicians, because adequate skills could enhance patient satisfaction, therapy compliance, symptom relief and cost effectiveness [9, 10]. The traditional mode of teaching these skills in ambulatory care is oral feedback from educators and peers on student consultation skills and professionalism. The effectiveness of written feedback from patients in medical student education has not been vigorously explored [6, 7, 11].

### Objectives and hypothesis

This study aims to examine whether additional patient satisfaction feedback to medical students after ambulatory consultations improves the medical students’ clinical consultation performance. We hypothesize that additional written feedback from patients to students, in the form of completed MISS-21 questionnaires, would improve both student performance in patient satisfaction scores (primary outcome) and clinical consultation skills, as reported by tutors (secondary outcome); and that the multisource feedback model increases patient satisfaction outcome in student consultations over time.

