### Interventions

Eligible students will be randomized in equal proportions to receive either patient satisfaction score feedback with usual verbal multisource feedback or usual verbal multisource feedback alone, as control.

Students in both the intervention and control group receive oral feedback from the tutor, PTA and peers immediately following each patient consultation. Both intervention and control groups receive immediate oral feedback according to the Rating Instrument of Clinical Consulting Skills (RICS) framework [13].

The educational intervention is written feedback using the 21-item Medical Interview Satisfaction Scale (MISS-21) in addition to the usual oral feedback [14]. The MISS-21 is a widely available 21-item validated visit-based questionnaire for measuring patient satisfaction in the primary care context. The MISS-21 questionnaire can be found in appendix 1 of the article by Meakin *et al.*
[14]. Students in the intervention group will receive their intervention pack no later than one week prior to the last consultation during one semester (generally six consultations in total). The intervention pack includes patient feedback questionnaires for all previous student-led consultations as well as written instructions about self-reflection on the feedback received based on the Pendleton feedback framework [15].

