### Data management and statistical methods

All data will be entered electronically. The dataset will be recorded in a spreadsheet maintained on a secured University server. All forms related to the study will be kept in locked cabinets. Access to the study forms and electronic data will be restricted. All reports will be prepared such that no individual participant can be identified.

All data will be analyzed using SPSS (IBM Corp. Armonk, NY, USA.) and Stata (StataCorp LP, College Station TX, USA). We will compare student characteristics between the two groups using a chi-squared test for categorical variables and a *t* test for continuous variables. We will model data using regression analysis to assess any change in mean score on the MISS-21 and RICS patient-centeredness subscale (dependent variables) at the first and last tutorial session for both groups and to determine whether any differences exist between intervention and control groups (independent variables), taking the following covariates into account: age, sex, education in years, postgraduate status and international student status. They may enter the regression model only if the covariates are imbalanced between the two groups after randomization due to chance.

Additional subgroup analyses will be performed for the following variables: undergraduate versus postgraduate study, work experience, local versus international students status and language spoken at home.

There will be no control group for patient assessors. We will use linear mixed effects regression to account for random effects of variability in student grouping and variability in patient characteristics.

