## Discussion

The results of this trial will inform educators whether multisource feedback with and without patient satisfaction feedback can improve student performance from baseline assessment in the intervention and control group respectively, and whether the educational intervention is effective in improving patient outcome and student performance compared with participants in the control group. This educational intervention will be replicable to other tertiary institutions.

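### The hypothesis that multisource feedback itself raises satisfaction over time cannot be tested, because both arms receive it and there is no comparator without it

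*Protocol article*

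**What the plan says.** The aim that opens Objectives and hypothesis concerns the added patient satisfaction feedback. The hypotheses that follow cover that contrast and then add a further one: "the multisource feedback model increases patient satisfaction outcome in student consultations over time".

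Two other places point the same way. The Discussion paragraph of the Abstract says the trial is meant "to assess the value of multisource feedback in teaching and learning about the management of ambulatory patients living with chronic conditions". The main Discussion describes what educators are to learn from the results: "whether multisource feedback with and without patient satisfaction feedback can improve student performance from baseline assessment in the intervention and control group respectively".

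The Interventions section fixes what each arm receives. Students are randomized to "either patient satisfaction score feedback with usual verbal multisource feedback or usual verbal multisource feedback alone, as control". It then states: "Students in both the intervention and control group receive oral feedback from the tutor, PTA and peers immediately following each patient consultation". Data management and statistical methods plans a regression whose first purpose is given as follows: "assess any change in mean score on the MISS-21 and RICS patient-centeredness subscale (dependent variables) at the first and last tutorial session for both groups". Its other purpose is to look for differences between the arms.

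**The concern.** The over-time hypothesis is causal: it says the feedback model increases satisfaction. The only evidence the trial can offer for it is the change from first to last session in students who all received that feedback. They are in their first clinical year and are followed for one semester and about six consultations, so some improvement is likely whatever feedback they get.

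If the plan is followed as worded, ordinary learning in that semester could be credited to multisource feedback. The Discussion presents the results as informing educators and the intervention as replicable elsewhere, so an unsupported conclusion could travel beyond this site.

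**Working it through.** **The plan's own figure.** The Sample size section gives 33 per group, 80% power, a difference of 0.32, SD 0.46 and 5% significance (taken here as two-sided). With the normal formula, n = 2(1.96 + 0.842)² × 0.46² / 0.32² = 32.4, rounded up to 33 per group. Power at 33 is 80.7% by the normal approximation and 79.5% by the exact *t* calculation. The figure reproduces. It covers the between-arm difference only and says nothing about the over-time hypothesis.

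**What the design identifies.** Between the first and last session, let M be the effect of oral multisource feedback, L the effect of everything else that happens to all students (other teaching, maturation, practice with the format), and W the effect of the written MISS-21 feedback.

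- Expected change, control arm: M + L
- Expected change, intervention arm: M + L + W
- Difference between arms: W

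M and L appear only as a sum. A control-arm rise of 0.20 fits M = 0.20 with L = 0 as well as it fits M = 0 with L = 0.20. Pooling the arms does not help and, with equal arms, adds W/2. The candidate covariates (age, sex, education, postgraduate and international status) are fixed student characteristics. The random effects concern student grouping and patients. Neither supplies a group with M absent.

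**How easily a rise would appear if M = 0.** Inputs:

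- SD 0.46 at both sessions. The protocol gives it for the control group; its use at both times is an assumption.
- Within-student correlation ρ from 0 to 0.7. This is not in the protocol and is assumed.
- Students treated as independent. This is a simplification, because they see patients in groups of three.
- A learning gain L of 0.10, 0.20 or 0.32 points. The first two are assumed; the last equals the trial's target difference.

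The SD of change is 0.46 × √(2(1 − ρ)), and the power of a paired *t* test at two-sided 5% comes from the noncentral *t*. Worked case: ρ = 0.5 gives an SD of change of 0.46. With 66 students the standard error is 0.46/√66 = 0.0566. A gain of 0.20 is then 3.53 standard errors, and the chance of a significant rise is 94%.

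| Learning gain L, with M = 0 | All 66 students, ρ 0 to 0.7 | One arm of 33, ρ 0 to 0.7 |
|---|---|---|
| 0.10 | 23–61% | 14–35% |
| 0.20 | 69–99% | 40–88% |
| 0.32 | 98–100% | 78–100% |

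These figures only illustrate the point. No sample size or analysis corrects them, because the missing element is a comparator.

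**The case against.** **The main question is sound.** The randomized contrast, the primary outcome and the sample size do not depend on the over-time clause, which comes last among the hypotheses. Study design calls the trial exploratory. All of this stands and limits the consequence. But an exploratory label does not supply a comparator, and it does not make a causal verb descriptive.

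**The wording is open.** The main Discussion asks whether performance can improve; it does not announce that it will. So the protocol does not commit to reporting a benefit. The difficulty is that the design cannot answer the question in either direction.

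**The mixed model deals with patients.** The plan includes random effects for student grouping and patient characteristics, so differing patients across sessions are at least partly addressed. Other teaching, maturation and practice are not.

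**Stronger readings the text does not support.** Because the Discussion speaks of improvement in the two arms respectively, a reader might infer that the intervention will be judged by finding one arm improved and the other not. The same sentence goes on to state a direct comparison with the control group. The Abstract, the Sample size section and the statistical methods also rest on a between-arm comparison. Comparing two within-arm tests would be an error, but it is not planned. A reader might also add regression to the mean as a rival explanation. The protocol has no exclusion criteria and does not select students on baseline score, so there is no reason to expect a shift in the mean from that source.

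**Conclusion.** The point holds for the over-time hypothesis and for the statements in the Abstract and main Discussion that would assess multisource feedback itself. Every student receives that feedback, so its effect cannot be separated from a semester of ordinary learning, and no planned analysis changes this. The conclusion follows from the allocation described in Interventions and needs no numerical assumption.

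The illustrative size does rest on assumptions: SD 0.46 at both sessions, correlation 0 to 0.7, independent students and a supposed learning gain. Under these, a gain of 0.20 points with no feedback effect gives a significant rise in 69–99% of trials of 66 students.

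The randomized comparison of written MISS-21 feedback is untouched. The text should be corrected because it states a hypothesis the trial cannot test; the trial's primary result is not in doubt on this account.

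**What to change.** - **Objectives and hypothesis:** restate the over-time clause as a descriptive aim, namely to report the change in MISS-21 from first to last session as means with confidence intervals, without causal wording.
- **Abstract (Discussion) and main Discussion:** limit causal conclusions to written MISS-21 feedback added to multisource feedback versus multisource feedback alone. Describe change since baseline in each arm as an observation that also reflects other teaching, maturation and practice.

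The cost is a few sentences and one secondary claim that the design cannot support. Randomization, outcomes, sample size and the between-arm analysis stay as they are. Keeping the causal claim would require a comparator without multisource feedback, which is a different trial.
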